#### Secondary efficacy endpoints

The secondary efficacy endpoints of this trial include the following:Incidence analysis: including the cumulative VAP incidence and the total number of VAP episodes and numbers and percentages of microorganisms causing VAPMortality analysis: including ICU, hospital, and day-28 mortality ratesTime analysis: including time to VAP onset from mechanical ventilation, delayed time to first VAP occurrence, mechanical ventilation duration, the number of ventilator-free days until day 28, and ICU and hospital lengths of stayEnteral feeding and nutritional status: including the proportions of patients with at least one vomiting episode, prokinetic treatment, and diarrhea; the proportion of patients given 100% of the calorie target; cumulative calorie deficit from day 0 to day 7; and variations in serum albumin during the first week of enteral nutritionOrgan functioning: including score variations in Sequential Organ Failure Assessment (SOFA)Inflammatory level: including variations in serum C-reactive protein (CRP) levels during the first week of enteral nutritionICU-acquired infection: proportions of patients with ICU-acquired infections (bloodstream, urinary tract, catheter-related, and other infections); score variations in CPIS

We plan to collect data on organ dysfunction at baseline and at various time points during the study. All the six domains of the SOFA score, including respiratory, coagulation, hepatic, cardiovascular, renal, and central nervous system, will be documented. Vasopressors, sedatives, and renal replacement therapy will also be reported to assess organ dysfunction. VAP episodes are monitored during the whole study. New-onset VAP is diagnosed if new microbial culture results from distal respiratory specimens are different from those prior, and colonization is excluded.

#### Safety endpoints

The safety outcomes are major adverse tube-associated events (MATEs), including vital sign alert events (defined as HR, RR, or MAP fluctuating beyond the range of ± 15%, or pulse oxygen saturation declining to < 90%), the requirement for sedatives or analgesics during tube placement, vomiting, rhinorrhagia, misplacing into the thoracic cavity, gastrointestinal bleeding or perforation, and so forth.

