### Interventions

Patients who meet the enrollment criteria will be randomized 1:1 to either the PTF or the GTF group, receiving postpyloric or gastric tube feeding, respectively, with other treatments exactly the same.

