#### Endoscopic feeding tube placement

A nasogastric feeding tube is inserted by nursing staff for the control group. Currently, in our clinical practice, the postpyloric feeding tube can be established by self-propelled dynamics from the gut with the assistance of prokinetic agents [34–36] and using a rescued bedside tube placement method by ICU physicians when necessary [37]. However, despite the short learning curve [38] and easy availability of the methods mentioned above, especially in the advantage of some decision support tools [39, 40], we otherwise decided to employ the endoscopic approach to establish the postpyloric feeding tube promptly and reliably for the study group. Hence, experienced endoscopists must be equipped when participating centers are recruited. In most ICUs currently in China, no special endoscopists are regularly prepared. In this case, a training course on endoscopic postpyloric tube placement is established to equip the physicians to become experienced endoscopists in the ICU.

Detailed training protocol is attached as Supplementary Appendix 4 in this manuscript. The essential procedures of endoscopic tube placement are as follows:

Patients are provided with oxygen inhalation, and ECG and blood oxygen saturation are monitored. After the patient is narcotized, they take the left lying position. During the operation, no secretion could be left in the mouth. A lubricated nasointestinal tube, approximately 25cm deep, is inserted through the nostrils and sent to the gastric lumen by gastroscopy. The esophagus, stomach, and duodenum are observed to confirm the absence of lesions or obstruction. The head end of the nasointestinal tube is clamped with foreign body forceps, and it is slowly pushed into the descending part of the duodenum to fix the nasointestinal tube. The gastroscope is returned to the gastric cavity, and the foreign body forceps are released into the gastric cavity. After about three times, they are transported to about 20–40 cm below the Treitz ligament. After the nasointestinal tube is fixed, the gastroscope and the nasointestinal tube guidewire are withdrawn.

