#### Security set (SS)

The SS included all actual cases that have received at least one feeding tube placement after randomization, with the safety endpoints recorded. The incidence of adverse events is denominated by the number of patients in the safety set.

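### One listed safety event, needing sedatives or analgesics for tube placement, is a planned step of PTF placement, so as written it largely restates allocation

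*Protocol article*

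**What the plan says.** Safety of PTF is one of the two primary objectives of the protocol article. The Safety endpoints section names MATEs as the safety outcomes. It lists vital-sign alerts, "the requirement for sedatives or analgesics during tube placement", vomiting, nosebleed, misplacement into the chest, and gut bleeding or perforation, and it leaves the list open. Nothing in that section separates planned sedation from unplanned sedation.

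The section on endoscopic feeding tube placement gives the two arms different procedures. For the study arm, the investigators chose to "employ the endoscopic approach to establish the postpyloric feeding tube promptly and reliably for the study group". The steps are introduced with "The essential procedures of endoscopic tube placement are as follows", and one of them is "After the patient is narcotized, they take the left lying position". For the other arm, "A nasogastric feeding tube is inserted by nursing staff for the control group", and no sedation or analgesia step is described.

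The Security set section uses the safety set as the denominator for adverse-event incidence. It admits patients who "received at least one feeding tube placement after randomization, with the safety endpoints recorded". Table 2 schedules MATE evaluation at D1 and D2.

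**The concern.** An adverse-event component should record something that may or may not happen to a patient after allocation. Here one component is a scheduled step of the experimental procedure and has no stated counterpart in the control procedure. A PTF patient treated exactly as the protocol describes has this event, and a GTF patient treated as described does not.

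What is at stake is how one safety result is read. A table of major adverse events would show a large excess in PTF on this row by construction. If the events are also summed to an overall rate, this row would dominate the sum. The events that signal injury, such as bleeding, perforation, misplacement and desaturation, would then barely move it.

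**Working it through.** The article states no MATE rate, MATE power or MATE sample size, so there is no figure to reproduce. The check is a comparison of sections, followed by an illustration of size.

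**Sections side by side**

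| Item | PTF | GTF |
|---|---|---|
| Who places the tube, and how | Endoscopic placement | Nursing staff, nasogastric |
| Sedation or analgesia step described | Yes, unconditional | None |
| Same step listed as a MATE | Yes, no exception stated | Yes, if it occurs |

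PTF patients who never receive a tube fall outside the safety set, so they do not dilute the PTF rate. A PTF patient who ends up with a nurse-inserted gastric tube would dilute it. That is why the component is close to fixed by allocation rather than exactly fixed.

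**Size of the effect on an overall rate**

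Let q be the probability of at least one other MATE component, assumed equal in both arms, so that PTF adds no other harm. Let s be the share of an arm sedated or given analgesia for placement, assumed independent of the other components. Then

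P(at least one MATE) = 1 − (1 − q)(1 − s)

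and the PTF minus GTF difference is (1 − q)(s_PTF − s_GTF).

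Assumed ranges, none of them from the article: q from 5% to 50%, s_GTF from 0% to 20%.

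- *s_PTF = 100% (procedure followed as written).* The PTF rate is 100% for every q. GTF ranges from 1 − 0.95 × 1.00 = 5% to 1 − 0.50 × 0.80 = 60%. The excess ranges from 0.50 × 0.80 = 40 points to 0.95 × 1.00 = 95 points.
- *s_PTF = 80% to 90%.* PTF ranges from 1 − 0.95 × 0.20 = 81% to 1 − 0.50 × 0.10 = 95%. The excess ranges from 0.50 × (0.80 − 0.20) = 30 points to 0.95 × 0.90 = 85.5 points.
- *Heavier coding of sedation in GTF, s_PTF = 100% and s_GTF = 50%.* The excess ranges from 0.50 × 0.50 = 25 points to 0.95 × 0.50 = 47.5 points.

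**Would a test flag it?** The planned 924 patients give 462 per arm. Less the 10% loss allowance, this is 462 × 0.9 = 415.8, taken as 415; the true size of the safety set is not known. The smallest gap in the first two scenarios is 90% versus 60% (q = 50%, s_PTF = 80%, s_GTF = 20%). Its standard error is √[(0.90 × 0.10 + 0.60 × 0.40)/415] = 0.0282, so 0.30 is about 10.6 standard errors. Power at two-sided 0.05 is practically 100% in every scenario of the first two bullets, with no difference in any other harm.

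**After removing the component:** both arms have rate q, and the difference is 0 under the same assumptions.

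**The case against.** A reader might infer that PTF must show harm and that the trial cannot answer its safety objective. The article does not support this. Its MATE list is open-ended, and it never defines an endpoint of at least one MATE per patient, although it uses that kind of wording for VAP and for vomiting. The Data analysis section names no MATE test. If components are reported one by one, only the sedation row is distorted. Treatment-related AEs and SAEs are recorded, and Table 2 schedules SAEs and enteral-nutrition events apart from MATE. All of this stands, and it limits the point to the sedation row and to any overall rate that includes it.

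The word requirement might mean only sedation beyond what was planned, and the appendices on placement training and on AE criteria, which are not shown, may say so. The article's definition does not, and centres could code it differently. Nor does it help that narcotization comes before insertion, since it is a listed step of placement.

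All patients are intubated, so background sedation might be counted in GTF as well. That would shrink the gap, but the component would then be uninformative for another reason. The same holds if the Discussion's remark that all tubes are placed endoscopically were taken to cover GTF, which would contradict the placement section.

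A reader might also infer that the safety set loses failed endoscopies mainly from the PTF arm and so hides harm. The wording is ambiguous: a placement received may include an attempt, and a PTF patient given a gastric tube instead stays in the set. The Analyses set section describes non-insertion for both tube types. Neither the direction nor the size of any bias can be determined.

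Finally, the Interventions section's phrase "with other treatments exactly the same" is loose, but the Background and the placement section already disclose that the placement methods differ. It adds nothing to this point.

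**Conclusion.** The point holds for the MATE definition as written. The sedation or analgesia component is close to fixed by allocation. It would show an apparent excess of major adverse events in PTF regardless of true harm, and any overall MATE rate would approach 100% in PTF. Under the main assumptions (every PTF placement follows the described procedure, other components equal at 5% to 50%, 0% to 20% of GTF patients sedated for placement) the excess is roughly 40 to 95 points. These figures illustrate the mechanism and do not predict trial results, because the article gives no MATE rates.

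The defect lies in one component of one safety outcome and in any sum that contains it. The remaining components reported separately, AEs, SAEs and enteral-nutrition events stay interpretable, and the primary efficacy endpoint, randomisation and sample size are untouched. It still deserves correction before analysis because safety is a primary objective.

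**What to change.** Reconcile the Safety endpoints section with the placement section. Take protocol-planned procedural sedation or analgesia out of MATE and report it as its own row by arm; alternatively, keep the component but count only sedation or analgesia beyond the planned procedure. Base any overall MATE comparison on the remaining components. This changes what counts as an adverse event and says nothing about sedation practice. Sedation remains visible as a burden of the PTF strategy.

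Minor: word the safety set as patients in whom tube placement was attempted, and do not make entry depend on the safety endpoints having been recorded.

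The cost is a change of endpoint and analysis-set wording. If sedation is already recorded as a MATE component, removing it needs no new data; counting only sedation beyond plan needs a clear coding rule for the centres. The downside is that MATE rates become less comparable with reports that use the present list.

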### Adverse events and serious adverse events

All treatment-related adverse events (AEs) and serious adverse events (SAEs) should be recorded on eCRF. SAEs will be reported to the Institutional Ethics Committee within 24 h of study staff becoming aware of the events. The participants are provided with commercial clinical research insurance by the manufacturer of the study product. Determination criteria for AE and SAE are detailed in Supplementary Appendix 5.

The treating physician will be responsible for determining the causal relationship of the SAE as either definitely, possibly, possibly not, or definitely not study treatment-related, as well as unclassified.

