## Methods/design

### Study design

The VIP study is designed as a prospective, multicenter, open-label, randomized, parallel-group, GTF-controlled (PTF vs. GTF 1:1) superiority trial in 4 tertiary care hospitals. The participating sites in this study include medical/surgical, medical, surgical, or emergency ICUs (see Table 1 for details of participating centers). Patient enrollment is expected to last for up to 36 months. The end of the study is defined as the last follow-up of the last enrolled patient. The trial has been registered at chictr.org.cn (ChiCTR2100051593). We used the Standard Protocol Items: Recommendations for International Trials (SPIRIT) reporting guidelines [29], and the SPIRIT checklist is attached in the Supplementary appendixes.

**Table 1 Tab1:** Research settings and names of each ethics committee

Research setting	Ethics committee name	Hospital rank and location
Maoming People’s Hospital	Medical Ethics Committee of Maoming People’s Hospital	Tertiary, Maoming, Guangdong, China
Guangdong Provincial People’s Hospital	Medical Ethics Committee of Guangdong Provincial People’s Hospital	Tertiary, Guangzhou, Guangdong, China
General Hospital of Southern Theater Command	Medical Ethics Committee of General Hospital of Southern Theater Command	Tertiary, Guangzhou, Guangdong, China
Heyuan People’s Hospital	Medical Ethics Committee of Heyuan People’s Hospital	Tertiary, Heyuan, Guangdong, China

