28-day survival											**×**

Eligibility screening includes diagnosis, inclusion/exclusion criteria, urine pregnancy test for female, demographics, medical history, and physical examination

*CPIS* Clinical Pulmonary Infection Score, *EN* Eenteral nutrition, *MATE* Major adverse tube-associated event, *SOFA* Sequential Organ Failure Assessment score

^a^Intervention means postpyloric tube feeding

^b^D means day from enrollment

^c^N means day from enteral nutrion

^d^EN-related adverse events include abdominal distension, gastric retention, vomiting, diarrhea, and aspiration of gastric contents

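### Non-serious adverse events reach the eCRF only if treatment-related, in an open-label trial and in conflict with the trial's own schedule, so the overall AE incidence is open to differential attribution

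*Protocol article*

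**What the plan says.** The section on adverse events and serious adverse events gives the only general instruction on what goes into the case report form: "All treatment-related adverse events (AEs) and serious adverse events (SAEs) should be recorded on eCRF". It then says "The treating physician will be responsible for determining the causal relationship of the SAE as either definitely, possibly, possibly not, or definitely not study treatment-related", or unclassified. That duty is stated for SAEs. No assessor and no scale are given for non-serious AEs. The criteria for determining AEs and SAEs are in Supplementary Appendix 5, which is not shown.

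The section on the security set fixes how AE rates are calculated: "The incidence of adverse events is denominated by the number of patients in the safety set". Safety of postpyloric feeding (PTF) is one of the two primary objectives. The design is a "prospective, multicenter, open-label, randomized, parallel-group, GTF-controlled (PTF vs. GTF 1:1) superiority trial in 4 tertiary care hospitals".

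Other sections treat collection differently. Under Safety endpoints, "The safety outcomes are major adverse tube-associated events (MATEs), including vital sign alert events" and a list of further event types. Table 2 schedules evaluation of these tube events (MATEs), of feeding-related AEs and of SAEs. A Table 2 footnote explains that "EN-related adverse events include abdominal distension, gastric retention, vomiting, diarrhea, and aspiration of gastric contents". The nutrition support protocol has feeding intolerance recorded when its symptoms occur, in both groups.

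**The concern.** If relatedness decides whether an event is entered, it acts before any analysis, and an analysis plan cannot recover events that were never entered. In an open-label trial the judgement is made with knowledge of the arm. Here the arms look different at the bedside: one has an endoscopic placement in a narcotized patient, the other a tube inserted by nursing staff. The same event may not be called treatment-related equally often in both.

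The meaning of the term in the control arm is also unclear, because a footnote to Table 2 defines the intervention as postpyloric feeding. Staff could take treatment-related to mean related to PTF and have no clear standard for a patient fed into the stomach.

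At stake is the reading of the overall AE incidence, which serves a primary objective. A difference, or the lack of one, could reflect attribution habits rather than event rates.

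**Working it through.** No figure in the article depends on this rule, so there is none to reproduce. The check has two parts.

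**1. The sections side by side**

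| Event class | Where the article defines or schedules it | Relatedness condition stated there? |
|---|---|---|
| Tube events (MATEs) | Safety endpoints: a list of event types, with numeric limits for vital signs ("defined as HR, RR, or MAP fluctuating beyond the range of ± 15%, or pulse oxygen saturation declining to < 90"%). Table 2: D1 and D2/N1 | No |
| Feeding-related AEs | Table 2: D2/N1 to D28, fixed list in a footnote | No |
| Feeding intolerance | Nutrition support protocol, both groups | No |
| Vomiting and diarrhea | Also secondary efficacy endpoints | No |
| SAEs | Table 2: D1 to D28; causality scale extends to definitely not related | No, but the general rule is ambiguous |
| All other non-serious AEs | Only the general eCRF rule | Yes |

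Three things follow.

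- The filter clearly applies to non-serious AEs that are on no list.
- Listed events fall under two instructions. A diarrhea episode thought to be due to antibiotics would be entered by a site following Table 2 and could be left out by a site following the general rule.
- The MATE list is open-ended and its evaluation is marked only at D1 and D2/N1. A later non-serious tube event that is not on the feeding-related list has no stated route to the eCRF except the general rule.

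**2. How far attribution alone could move the AE incidence (illustration)**

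From the document: 924 patients randomized 1:1, so 924 / 2 = 462 per arm; two-sided P<0.05. Assumed, and not in the document: a true AE rate of 20% in both arms and the share of events judged related in each arm.

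Recorded rate in an arm = true rate × share judged related.

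P(P<0.05) ≈ Φ[(d − 1.96·SE0) / SE1], where d = p1 − p2, SE0 = √[2·p̄(1 − p̄)/n], SE1 = √[p1(1 − p1)/n + p2(1 − p2)/n], and p̄ is the mean of p1 and p2.

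Worked case, 40% versus 30% judged related: p1 = 0.20 × 0.40 = 0.08; p2 = 0.20 × 0.30 = 0.06; d = 0.02; SE0 = 0.01679; SE1 = 0.01677. Then (0.02 − 1.96 × 0.01679) / 0.01677 = −0.77, and Φ(−0.77) = 0.22.

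| Judged related, PTF vs gastric | Recorded rates | Recorded ratio | P(P<0.05), 462 per arm | P(P<0.05), 416 per arm |
|---|---|---|---|---|
| 50% vs 50% | 10% vs 10% | 1.00 | 5% | 5% |
| 60% vs 50% | 12% vs 10% | 1.20 | 16% | 15% |
| 40% vs 30% | 8% vs 6% | 1.33 | 22% | 20% |
| 50% vs 30% | 10% vs 6% | 1.67 | 61% | 57% |
| 50% vs 25% | 10% vs 5% | 2.00 | 82% | 78% |

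The last column applies the planned 10% loss (462 × 0.9 ≈ 416). If attribution is equal in both arms, no spurious difference arises.

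**The case against.** The strongest reply is that the safety data that matter are already collected without a filter. The only declared safety outcomes are MATEs, named by event type and partly by numeric limits. Feeding-related AEs are a fixed list on a schedule. SAEs are evaluated to D28, and a causality scale that includes definitely not related makes sense only if unrelated SAEs are captured. This stands. A reader might infer that the whole safety comparison is filtered by attribution, and the article does not support that.

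A reader might also infer that the treating physician, knowing the arm, decides which non-serious AEs count. The article gives that physician the causality judgement for SAEs only ("The treating physician will be responsible for determining the causal relationship of the SAE"). Extending it to non-serious AEs is a guess, and Appendix 5 may say more. What remains is that the judgement which decides entry has no named assessor in the article.

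The security-set section fixes a denominator and states no test between arms. The data analysis section applies a chi-squared test to incidence outcomes in general without naming AEs. So a formal comparison of overall AE incidence is likely but not stated.

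Finally, a general rule and a schedule of named events can coexist, with the schedule supplementing the rule. That is a fair reading, but the article does not say so. The rule is the only general eCRF instruction, and it is the narrower of the two.

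**Conclusion.** The point holds within limits. As written, non-serious AEs outside the listed categories are entered only if treatment-related, in an open-label trial, so the overall AE incidence on the safety set has a numerator open to differential attribution. For MATEs, the listed feeding-related events and SAEs, the article does not clearly impose a filter, but its sections give different instructions and must be reconciled.

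The size is unknown. The illustration runs from 5% (equal attribution) to about 82% (50% versus 25%) for a spurious P<0.05, and every attribution share and the 20% rate are assumptions. The figures show that the mechanism can matter, not that it will. They do not apply to event types collected whatever their attribution. The conclusion rests on the recording sentence as printed; Appendix 5 could clarify definitions, but the sentence itself would still need correcting.

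**What to change.** In the section on adverse events and serious adverse events, replace the recording sentence with one stating that the following are recorded in both arms regardless of judged relationship:

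- the feeding-related events listed under Table 2;
- the tube events listed under Safety endpoints, including those occurring after D2;
- all SAEs.

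Define the AE incidence in the security-set section, and any between-arm comparison, on these all-cause events. Keep causality as a separate, descriptive field. If other, unlisted AEs are still collected only when judged related, report them descriptively and do not compare them between arms.

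The cost is a wording change to the protocol and eCRF and some extra entries. Evaluation of feeding-related events and SAEs is already scheduled to D28; the main addition is tube events after D2. Recruitment is under way, and unrecorded events are hard to recover, so the change is worth making soon.
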